**Fig 1 pone.0278428.g001:**
[figure not shown]
Proposed referral pathways for players with injuries or illnesses during the FIFA football nurse intervention.

Current team medical practice; knowledge and practice of injury prevention strategies, injury risk; and mental health assessment will be assessed at the beginning, halfway through and at the end of the season. Football exposure; injuries, illnesses, and medication use surveillance will be recorded after every training session or match event throughout the season.

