*Mental health assessment*. This will be assessed using the Sports Mental Health Assessment Screening Tool-1 (SMART-1). The SMART-1 is a standardised assessment tool that aims to identify individual athletes potentially at risk for or already experiencing mental health symptoms and disorders to facilitate timely referral for those in need of support or treatment [42].

*Football exposure*: *Injury*, *illness*, *and medication use surveillance*. These data will be collected at a cluster level using injury, illness and football load forms as recommended in injury consensus statements [36]. The research team will follow up with each football nurse on a weekly basis to ensure surveillance data is being captured. Should an injury occur that requires investigations or further management, the nurses will refer to the PT/Dr, who will proceed with the treatment, design/prescribe further management and document accordingly. League performance will also be collated from FAM at the end of the season as this has previously been associated with injury rates in other team sports [43].

Assessment of injury behaviours, team medical practice, injury risk, nutritional data, and mental health assessment will be done at three time points: at the beginning before the trial begins, halfway through the trial, and at the end of the season. Football exposure and surveillance data will be collected and collated at the end of each training session and/or match until the end of the season.

*Measurement of potential confounders*. Despite all players playing in the same league and at the same level, primary confounders for injury risk include physical/ anthropometric characteristics; existing mental health or psychiatric conditions and home environment, which may influence the SMHAT- 1 values, for example. Secondary confounders include playing experience, playing position, and playing level as well as socio-economic status, which will affect nutrition, menstrual hygiene management and private management of injuries. Where possible, these will be considered in the analyses. Some of them will also be explored further in the qualitative interviews at closure of the protocol.

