For the injury, illness, and medication use data, injury, illness, or medication use history will be recorded to determine the baseline injury, illness, or medication use risk. Injury, illness, and medication use rates and corresponding 95% CIs will be calculated for all players as the number of injuries/illnesses/medications reported per 1000 hours of football exposure (training and match). The severity of the injuries/illnesses, as scored by the number of days of missed training or matches, will also be calculated. Additional analysis will include, but not be limited to, the incidence and type of injury/illness/medication; chronic versus acute injuries/illnesses/medications; contact versus non-contact injuries and mechanism of injury (all per 1000 player hours). A Poisson regression will be used to compare differences in the injury, illness, or medication use rates between the control and intervention arms. To evaluate the impact of the FIFA Football nurse intervention on injury/illness/medication use outcomes, we will use logistic regression analysis to compare the proportion of players with injuries/illness/taking medications between the intervention and control arms, adjusting for potential confounding variables such as previous injury, age, playing experience, BMI, and playing conditions. We will also conduct subgroup analyses to determine whether the intervention has differential effects on different subgroups of players.

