*Patient and public involvement*. Patients and the public were not involved in the design of this protocol. However, various stakeholders in Malawi women’s football (e.g., nurses, women football players, district sports officers, district representatives in women’s football) will be consulted on the conduct, reporting, and dissemination plans for the research.

*Project time frame*. This project will be performed over an 8-month period during the 2022/2023 football season (May to December).

May 2022 –training of nurses; recruitment of football teams; randomisation of teams.June 2022 –baseline testing of teams (assessment of injury behaviours, team medical practice, injury risk, nutritional data, and mental health assessment)June 2022 to December 2022 –implementation of the football nurse intervention; injury surveillance; adherence and exposure data collection.October 2022 –midway testing of teams (assessment of injury behaviours, team medical practice, injury risk, nutritional data, and mental health assessment)December 2022 –final testing of teams (assessment of injury behaviours, team medical practice, injury risk, nutritional data, and mental health assessment); semi-structured interviews with sample of players and coaches from both groups and all nurses

*Outcomes and significance*. We expect to develop a low cost, sustainable and context relevant solution to manage the treatment gap of football injuries/illnesses in underserved communities such as women’s football. Through the study, we also anticipate the development and maintenance of player health, injury and illness monitoring databases for Malawian women football players in club football, which can be replicated in grassroots women’s football leagues in LMICs. This will allow the monitoring of trends and development of relevant preventive or management strategies in these settings. Additionally, we expect this study to lead to the development of a flagship model which can inform implementation of similar task sharing approaches to SEM practice in other LMICs in Africa and globally.

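### Severity counted as days of training or matches missed, with surveillance ending at season end, cuts long absences short and, read literally, depends on team timetable

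*Protocol article*

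**What the plan says.** The Data analysis section gives a scoring rule for severity: "The severity of the injuries/illnesses, as scored by the number of days of missed training or matches, will also be calculated". In the same paragraph, event rates are scaled to 1000 hours of exposure, but no scaling is stated for severity.

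Three places fix when the data are collected:

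- The Football nurse intervention section, after Fig 1, says that exposure and surveillance data "will be recorded after every training session or match event throughout the season".
- The Secondary outcome measures section says: "Football exposure and surveillance data will be collected and collated at the end of each training session and/or match until the end of the season".
- The Project time frame lists "June 2022 to December 2022 –implementation of the football nurse intervention; injury surveillance; adherence and exposure data collection".

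The article describes no follow-up of unresolved injuries or illnesses after the season. The Trial design section says in general terms that surveillance follows the latest injury consensus statements, but it states no severity rule.

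**The concern.** Severity should reflect how long a player was unavailable. The stated rule lets two other things into the score.

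The first is the calendar. Collection stops at season end, so an absence still running then contributes only the days seen so far. The loss grows with the true length of the absence, so the measure is weakest for serious injuries. Those are the cases that the nurses are expected to refer to their supervising physiotherapist or doctor.

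The second arises if the wording is taken literally. A day then counts only if training or a match took place and the player missed it. The Recruitment section describes the league as amateur, and no common training timetable is given. Two teams could give different scores to the same absence.

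What is at stake is the descriptive account of how serious injuries and illnesses were in teams with and without a nurse.

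**Working it through.** The article gives no figure for severity, so there is nothing to reproduce. The check takes the stated rules and asks what they do to an absence of known length.

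**Inputs**

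- Collection window: June to December 2022 (Project time frame). Exact dates are not given. Assuming 1 June to 31 December, L = 214 days.
- True absence in calendar days, D: not in the article. Illustrated with 28, 90 and 180.
- Onset: assumed uniform over the window.
- Football days per week, s: not in the article. Assumed to run from 2 to 6.

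**Season end (applies on either reading of days)**

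An absence is truncated if it starts within D days of the end. With uniform onset:

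- share truncated = D / L
- mean shortfall as a share of the true length = D / (2L), because truncated absences lose half their length on average

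| D | Share truncated | Mean shortfall |
|---|---|---|
| 28 | 28/214 = 13% | 28/428 = 6.5% |
| 90 | 90/214 = 42% | 90/428 = 21% |
| 180 | 180/214 = 84% | 180/428 = 42% |

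A day-by-day count over the 214 days, run for 28 and 180 days, gives nearly the same shortfalls: 6.3% and 41.8%.

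The window could be shorter, because baseline testing also falls in June. If surveillance started on 1 July, L = 214 − 30 = 184. The truncated shares become 28/184 = 15% and 90/184 = 49%, with mean shortfalls of 28/368 = 7.6% and 90/368 = 24%.

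**Timetable (literal reading only)**

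For an absence that ends within the season, score = D × s / 7. For D = 28:

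| Football days per week | Score |
|---|---|
| 2 | 28 × 2/7 = 8 |
| 3 | 28 × 3/7 = 12 |
| 5 | 28 × 5/7 = 20 |
| 6 | 28 × 6/7 = 24 |

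This is a threefold range for the same absence. If days means calendar days of unavailability, the timetable effect disappears and the season-end effect stays.

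**The case against.** The strongest reply is that the phrase can mean ordinary time loss in calendar days, and that the Trial design section ties surveillance to consensus definitions and procedures. The forms are not shown and may already hold a return date. How open cases are coded, and by which method they are summarised, is detail that an article may leave to fuller documents.

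Much of this stands. The timetable effect depends on the literal reading, and its size is unknown because no training frequency is given. It cannot be assumed that the forms lack a return date. However, the general appeal to consensus statements gives no severity rule, while the Data analysis section gives its own. Nor does that appeal lift the stated end of collection. The point concerns a rule and a stopping time that the article states.

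A reader might infer more than the text supports:

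- **Serious late injuries score near zero.** This fits only the last days of the season. Under uniform onset, 7/214 = 3% of injuries start in the final week. Earlier serious injuries are shortened but not erased.
- **Open absences are coded as completed, or a mean will be reported.** The article says neither. It says only that severity will be calculated.
- **The comparison of arms is biased.** This is not shown. All teams play in one league, allocation is drawn within region, and the window is the same for both arms. Nothing suggests that having a nurse changes training frequency.
- **This is the only information on seriousness.** Referral and treatment are a separate objective, and supervisors document the cases referred to them.

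**Conclusion.** The concern holds as a measurement flaw of limited weight. Taken together, the scoring rule and the season-end stop shorten absences that are still open in December, whichever way days is read. The shortfall is small for short absences (6.5% on average at 28 days) and substantial for long ones (21% at 90 days, 42% at 180 days). These figures rest on the assumed 214-day window, uniform onset and chosen absence lengths. The article does not say how common long absences will be. The dependence on timetable follows only from the literal wording.

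Severity is a secondary, descriptive measure with no stated test between arms. The rate and proportion comparisons in the Data analysis section are not stated to use it. The primary outcome, team sports medicine practice, is unaffected. The change is worth making because it is cheap and because, without a return date or an open-case flag, a truncated absence may be impossible to tell from a completed one afterwards.

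**What to change.** 1. Define severity as calendar days from onset to return to full training or match availability. This defines a measurement only and does not say when a player should return.
2. State how this definition fits the consensus statements invoked under Trial design, so that one rule applies throughout.
3. Make sure the injury and illness forms hold a return date, or a not-yet-returned flag completed at the existing December assessment.
4. Treat open cases as right-censored at that assessment and summarise severity by arm as time to return, for example with Kaplan-Meier curves or median time to return. Do not count them as completed absences.

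The cost is at most one form field, a sentence or two of protocol text and slightly more analysis. No extra visit is needed.

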### Trial design and study arms

#### Trial design

This study will be a cluster randomised controlled trial. This design is applicable as it allows for a field-based intervention to be implemented for one competitive season while decreasing the chances of contamination between the groups. African women’s football is the sport that has been chosen as it is the most commonly played women’s team sport on the continent and therefore, is a priority sport for improving medical care at and from grassroots levels. Adherence to the FIFA Football Nurse program; football exposure data; injury, illness and medication use surveillance and the in this trial will be similar to those used in previous football studies [35, 37] and conform with the definitions and data collection procedures outlined in the latest injury consensus statements [36]. The study will also include a qualitative evaluation of the participants’ (players, coaches, nurses) experience of the FIFA football nurse program.

All the 24 women’s teams in the Malawi Women’s Super league will be randomly assigned in a 1:1 ratio to either the Football Nurse intervention (INT–12 teams) or the control group/standard care (CON–12 teams) through a random draw. For the allocation schedule for random assignment to each arm, the names of the 24 teams will be placed in three (3) bowls, a bowl for each region. They will then be picked consecutively and alternately, and allocated into the INT and CON groups by one of the investigators ([name]). This will be done after the training of the nurses and after each team (cluster) have agreed to be a part of the study. For transparency, the random draw will be conducted in the presence of representatives from the football association and will be video and audio- recorded.

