#### Sample size

The study aims to evaluate the impact of the Football nurse intervention on team sports medicine practice. Hence, the study will recruit twelve (12) nurses, with one assigned to each intervention team, and six (6) physiotherapists and/or doctors to supervise the Football Nurses from two teams each.

To determine the appropriate sample size, the study used the cluster randomized formula as in previous studies [38]. This formula considers the intra-cluster correlation coefficient, number of participants, expected effect size, and power of the study. The formula is as follows:

$$C=1+{\left(Z_{\alpha /2}+Z_{\beta }\right)}^{2}\frac{\left[\sigma_{0}^{2}+\sigma_{1}^{2}\right]\times [1+(m-1)k]}{m{\left(\mu_{0}-\mu_{1}\right)}^{2}}$$

Where C is the number of clusters required per treatment arm, *Z*_*α*/2_ and *Z*_*β*_ are the critical values of the standard normal distribution for the desired confidence level and power, respectively, *m* is the number of individuals per cluster and *k* is the intracluster coefficient, *μ*_1_ and *μ*_0_ are the true means, and σ_1_ and σ_0_ are the standard deviations, of the outcome variable in the presence and absence of the intervention, respectively.

The design effect of a CRT is related to the intracluster correlation coefficient as follows:

DEFF=1+(m−1)k

Assuming a 95% confidence level (*Z*_*α*/2_ = 1.96), a power of 80% (*Z*_*β*_ = 0.84), an expected effect size of 0.19 (based on a 50% increase in team sports medicine practice), a standard deviation of 0.30, an intra-cluster correlation coefficient of *k* = 0.2, and 25 participants per cluster, the study estimates that it will need 12 clusters (teams) in both the control and intervention groups. Therefore, a total of 600 participants will be recruited, with 300 participants in each group. In summary, the study will recruit twelve (12) nurses and six (6) physiotherapists/doctors to supervise the intervention teams. The study will need 12 clusters (teams) in both the control and intervention groups, with a total of 600 participants (300 in each group) to detect a statistically significant change in team sports medicine practice at a 95% confidence level and 80% power, using the cluster randomized formula [38, 39].

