For the testing data such as injury risk (FMS, musculoskeletal screening), nutritional data (24h recall), and mental health assessment (SMHART-1), a mixed between-within-subjects ANOVA will compare the two arms over the whole intervention, then a post hoc Bonferroni test will be used to determine whether there are significant changes in the various scores and at what time point during the intervention these occur. Should there be a significant change in test scores, a one-way ANOVA will be performed at the specific time point to determine which specific test is different between arms. Additionally, a mixed effects logistic regression model will be used to examine the effects of arm assignment (intervention vs control) and time for categorical outcomes (e.g., sports injury prevention behaviours). To assess adherence and feasibility, descriptive statistics will be used to determine which aspects of the FIFA Football Nurse programme are best or worst implemented. Sensitivity analyses include adjustment for baseline team sports medicine practice and other potential confounding factors (e.g., previous injury, age, football experience, BMI, socioeconomic status). We will also include tests for effect-modification by relevant factors.

Additionally, data from the semi-structured interviews will be transcribed verbatim and a thematic analysis will be conducted using Braun and Clarke’s 6 step model [44] to group common themes and describe the experiences of women’s football stakeholders, and the barriers and facilitators towards the football nurse task-sharing approach. Analysis will be approached inductively by tagging meaning units which will then listed as themes, compared, and clustered to form categories, then assigned as general dimensions. Inter-rater reliability checks will be conducted by a blinded researcher, who will code a subset of the manuscripts and determine congruence of resulting themes. If clustering effects are observed in the data, these will be accounted for using appropriate statistical methods such as multilevel or hierarchical models.

All statistical tests conducted in this trial will be two-sided and p-values of < 0.05 will be considered statistically significant.

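### Illness and medication-use history are recorded to set baseline risk but are not named as covariates for their own outcomes, and the Poisson rate comparison names no covariate, which costs precision

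*Protocol article*

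**What the plan says.** The relevant text is the Data analysis part of the protocol article, printed under Secondary outcome measures.

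- **What is recorded.** "injury, illness, or medication use history will be recorded to determine the baseline injury, illness, or medication use risk". All three histories are collected, and the stated purpose is baseline risk.
- **Rates.** "A Poisson regression will be used to compare differences in the injury, illness, or medication use rates between the control and intervention arms". No covariate is named.
- **Proportions.** One logistic specification covers players injured, ill or taking medication, "adjusting for potential confounding variables such as previous injury, age, playing experience, BMI, and playing conditions". The covariates are introduced as examples, so the list is open.
- **Elsewhere in the same section.** The baseline comparability checks name injury risk but not illness or medication use. The sensitivity analyses again give previous injury as the only individual history, also as an example. They do add the baseline of the primary outcome, team sports medicine practice.

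Illness history and medication history are not named as covariates anywhere in the article.

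**The concern.** For injury, the logistic list names the matching history. For illness and medication use it names the history of a different outcome, although the matching one is said to be recorded. An analyst working from the text as printed would fit the illness and medication models with previous injury and without their own baseline, and would fit the rate models with no baseline at all.

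The principle of adjusting for an outcome's own baseline is already accepted in the sensitivity analysis of the primary outcome. It matters more than usual here because whole teams are allocated, 12 per arm. Existing illness or medication use may cluster by team, so the arms can differ noticeably at the start by chance. Previous injury is unlikely to stand in well for that difference. What is at stake is the width of the interval for these secondary comparisons, and how a result should be read if the draw happens to be uneven.

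**Working it through.** **The plan's own figure.** The article gives no precision or size calculation for illness or medication use. Its only calculation is for the primary outcome. The Sample size section takes "an expected effect size of 0.19 (based on a 50% increase in team sports medicine practice", together with SD 0.30, ICC 0.2 and 25 players per team. The printed formula gives

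C = 1 + (1.96 + 0.84)² × (0.30² + 0.30²) × [1 + 24 × 0.2] / (25 × 0.19²) = 1 + 7.84 × 0.18 × 5.8 / 0.9025 = 10.07,

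which rounds up to 11 teams per arm against the stated 12. The stated number is on the safe side, and nothing below depends on the gap.

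**Inputs for the check.**
- From the article: 12 teams per arm and m = 25 players per team. ICC = 0.2 is stated for the primary outcome only and is borrowed here.
- Assumed, because the article gives no values: baseline medication use p, the ICC for medication use (0.05 to 0.2), and persistence, meaning season use among baseline users against others.

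**Step 1: chance difference between arms at baseline.** SD of the arm difference = √{p(1−p)[1+(m−1)ICC]/m} × √(2/12).

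| p | ICC | SD (points) | 95% range (points) |
|---|---|---|---|
| 0.1 | 0.05 | 3.6 | ±7.1 |
| 0.2 | 0.05 | 4.8 | ±9.5 |
| 0.2 | 0.2 | 7.9 | ±15.4 |
| 0.3 | 0.2 | 9.0 | ±17.7 |
| 0.5 | 0.2 | 9.8 | ±19.3 |

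**Step 2: carry-over into the season.** Take p = 0.2, ICC = 0.2, season use 70% in baseline users and 30% in others, and no nurse effect. The baseline difference alone then moves the season difference by up to 1.96 × 0.079 × 0.40 = 0.062, about ±6 points.

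**Step 3: precision with and without own baseline, on team proportions.**
- Team baseline variance: 0.16 × 5.8/25 = 0.0371.
- Season team variance: 0.40² × 0.0371 + 0.21/25 = 0.0059 + 0.0084 = 0.0143.
- SD of the arm difference without baseline: √(0.0143/6) = 0.049.
- With baseline removed: √(0.0084/6) = 0.037, or about 0.038 after the lost degree of freedom, as simulation also gave.
- Reduction: about 23% (22% from the rounded figures, 1 − 0.038/0.049). At ICC 0.05 the simulated reduction is 9%.

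More generally, interval width shrinks by about 1 − √(1−r²), where r is the team-level correlation of baseline with season use: 5% at r = 0.3, 13% at 0.5, 29% at 0.7.

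**Step 4: error rates.** In 4,000 simulated null trials per setting (p = 0.3, ICC 0.2, persistence 60%/17% or 80%/10%), both analyses averaged zero difference and rejected close to 5% overall. A baseline imbalance above 9 points arose in 31% to 32% of trials. Within those, the comparison without baseline showed a mean spurious difference of 5.9 to 9.6 points and rejected in 13% to 16%. With own-baseline adjustment the difference was about zero and rejection about 5%.

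**The case against.** **The list is open.** A reader might infer that the plan rules out illness and medication history and adjusts for previous injury in their place. The text does not say that: both covariate lists are given as examples, and the article says elsewhere that confounders will be considered where possible. A full list per outcome may sit in an analysis plan that is not shown. This stands, and it limits the point to what is named. It does not remove the point, because the article does name one history for all three outcomes and passes over the two matching ones that it says are recorded.

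**No validity problem.** A reader might infer bias or an inflated false-positive rate. The check shows neither. An unadjusted comparison of randomised teams is legitimate, and a correct team-level interval already allows for chance baseline differences. This stands in full.

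**No special shortage of units.** Nor do illness and medication use rest on fewer independent units than the other outcomes. All rest on the same 24 teams.

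**The size is assumed.** Prevalence and persistence have no source in the article, and the ICC is borrowed from the primary outcome. Only medication was modelled, and illness may persist less. The comparison was with no adjustment, whereas the logistic model already carries several covariates. The draw is made within regions ("the names of the 24 teams will be placed in three (3) bowls, a bowl for each region"), which the simulation ignored. All of this stands, and it makes the percentages illustrative.

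**Ascertainment.** The Project time frame puts the draw in May and baseline testing in June. Under Standardisation of procedures, nurses are mainly responsible for data collection in intervention teams, while the research team works through a designated team member in control teams. History taken after allocation by different kinds of collector could differ by arm, and adjusting for it could then add bias. This narrows the fix but does not defeat it: past medical history is described as a self-administered questionnaire, and the planned adjustment for previous injury is exposed to the same risk.

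**Conclusion.** The point holds in a limited form. The article records illness and medication-use history to determine baseline risk, but does not name either as a covariate for its own outcome. It names no covariate for the Poisson rates.

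The consequence is lost precision, and chance imbalance that remains in whichever draw is made. For medication use, with 20% baseline use, 70%/30% persistence and no other adjustment as comparator, own-baseline adjustment cuts the SD of the arm difference by about 9% at ICC 0.05 and 23% at ICC 0.2. These figures are for differences in team proportions, not for log odds ratios or rate ratios. The added gain over the planned logistic covariates, and any gain for illness, cannot be worked out from the article.

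These are secondary outcomes, so the matter is modest. It is still worth correcting: all 24 teams of the league are already in the trial, so precision cannot be bought with more clusters, and naming the covariate now avoids choosing it after the results are seen.

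**What to change.** In the Data analysis paragraph on injury, illness and medication use, replace the single history term by the history of the same outcome: previous injury for injury, previous illness for illness, prior medication use for medication. Name it in both the Poisson and the logistic comparison. Where team summaries are analysed, enter it as the team's baseline proportion or rate.

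Add two conditions. The history must refer to the period before the draw. It must be collected by the same self-administered questionnaire in both arms, not elicited by the nurse in one arm and through a team contact in the other. The description of that questionnaire mentions injury and medical history, so confirm that it also asks about medication use.

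The cost is a short change of wording and one degree of freedom per model. The histories are already planned, and the number of teams does not change.
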